#### Time since vaccination.

If the sample size allows it, the time since completion of the high-dose influenza vaccine will be analysed as a secondary objective. For the rIVE estimation, time since vaccination will be considered a confounder to add to the model. For the absolute IVE estimation, time since vaccination will be calculated at each time point and classified into the following categories:

From time 14 days to ≤ 89 days after time 0 (i.e., < 13 weeks, approximately 3 months);90–179 days after time 0 (i.e., ≥ 13 weeks and < 26 weeks, approximately 3–6 months);180–272 days (i.e., ≥ 26 weeks and < 39 weeks, approximately 6–9 months).

### Outcome

The outcomes of interest are defined based on the primary cause of admission to a hospital, coded according to ICD-10, J11 (Influenza with pneumonia).

As a secondary outcome, we will also analyse cardiorespiratory hospitalisations as a primary cause of admission, with a secondary diagnosis of pneumonia, J12 (Viral pneumonia) and J18 (Pneumonia of unknown etiology).

Each of these outcomes will be analyzed separately. The outcome date will correspond to the hospitalisation date. Details on the ICD-10 codes are available in the Supplementary S1 Table.

### Stratification variables

If possible, and when applicable, rIVE will be estimated for each seasonal campaign.

### Potential confounding variables for adjustment

A set of variables will be used to account for confounding bias. Sociodemographic variables, such as sex, age, health administrative region, and the European Deprivation Index, will be used as potential confounding factors. We will also consider the vaccination against COVID-19 in the previous season to account for health-seeking behaviour. The presence of chronic conditions, such as diabetes, asthma, or other chronic respiratory diseases, cancer, chronic renal disease, hypertension or other chronic cardiovascular disease, obesity, chronic hepatic disease, neuromuscular disease, and immunodeficiency, will also be included as potential confounding factors.

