### Data sources

The study will use routinely collected data from various population health registries with national comprehensive scope. Each database contains a unique identifier for each individual to allow data linkage between databases. We have not yet received any access to the data at the time of submission of this study protocol but have previous experience in studies using this approach [1–6]. The National Health Service User (NHSU) dataset is the reference population database and includes individual records of the target study population. For this study, we will only consider individuals who had contact with the NHSU healthcare system three years before the start of the study period to account for health seeking behaviour and likelihood to have a vaccine recommended. Vaccination registry or vaccination record databases with individual data, including influenza and vaccine brand dates, will be provided by the National Vaccination Registry – VACINAS. VACINAS is the national vaccination registry, that is accessible to all health professionals who administer the vaccine (in both the public and private sectors) and vaccine registration is mandatory. Primary healthcare data on diagnoses, chronic conditions, and eligibility for the influenza vaccine - SIM@SNS, which is the data platform for patient management at PC. Regarding the outcome, the National Hospital Discharges Registry will be used to assess hospitalisation information (BDMH and BIMH), which is used for public hospital management and centralizes data from mainland Portugal. Hospital discharge codification is conducted by trained medical doctors using ICD-10 codes.

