#### Propensity score matching.

Individual characteristics might influence vaccination status, leading to systematic differences between those vaccinated with different vaccines and those vaccinated (rIVE) and unvaccinated (absolute IVE). Propensity score matching is a statistical technique used to reduce selection bias in observational studies by creating a matched set of treated (vaccinated with high-dose influenza vaccine) and untreated (vaccinated – rIVE and unvaccinated – absolute IVE) individuals with similar propensity scores. The first option will be matching without replacement, 1-to-1. However, considering the vaccination coverage, this ratio might need to be reviewed.

Several assumptions should be met to ensure that conditioning on the propensity score will lead to unbiased estimates of average treatment effects. The first one is that there should not be unmeasured confounders, i.e., the variables affecting vaccination status and hospitalisation due to influenza-like-illness should have been measured. The second relates to positivity, each individual should have a non-zero probability of getting the high-dose influenza vaccine. Additionally, the propensity score model should be correctly defined, and there should not be any interference between individuals, i.e., an individual vaccinated with the high-dose influenza vaccine will not affect the hospitalisation of another individual. This final assumption has implications in estimating absolute IVE studies due to herd immunity since vaccinated individuals could indirectly protect unvaccinated individuals, leading to IVE underestimation. To account for potential violations of this assumption, we will consider statistical methods that account for clustering, which could be the geographical region of residence.

The propensity score will be estimated using logistic regression, where the vaccination status will be the outcome, and the baseline individual characteristics will be used to adjust. Then, the vaccinated with high-dose influenza vaccine and vaccinated (rIVE) or unvaccinated (absolute IVE) individuals with similar propensity scores will be matched, using nearest neighbour matching, and compared to ensure the balance of covariates. Once the balanced dataset is obtained, the Cox proportional hazards regression model will be used, with the adjustments mentioned in the section above to adjust for residual confounding [13].

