Despite its strengths, this study also has some limitations. We plan to use EHR, which does not aim to collect data for research purposes. Thus, this could lead to misclassification bias regarding vaccine status, outcomes, and confounding variables. For this reason, we might be unable to control for residual confounding since many relevant variables are not monitored or available in registries, and one should be aware that estimates can vary in the presence of confounding. Additionally, unvaccinated individuals will be the reference group when estimating absolute IVE. However, these individuals might differ from the vaccinated individuals due to their clinical profile or possible misclassification bias. Thus, we will use propensity score matching to account for this, assigning a probability of being vaccinated to each individual based on covariates. Considering that we will use EHRs, we might also be unable to correctly identify all individuals living in LTCF, as the report might vary geographically and temporally. Additionally, identifying these individuals might be associated with a differential bias, assuming that vaccinated individuals might be more likely to be reported as living in LTCF than unvaccinated. This situation is less likely to be problematic when estimating relative and absolute IVE in the community.

Another limitation is the potential outcome misclassification. In VE studies, it is extremely important to have sensible outcome definitions as the vaccines are designed to protect against influenza and related complications and studies use laboratory-confirmed outcomes. Using specific influenza ICD codes to identify severe influenza could underestimate severe influenza as the diagnosis is highly dependent on the testing strategy and, thus, on the codification attributed at discharge. On the other hand, including a broader range of ICD codes in the outcome definition could also underestimate IVE by including non-influenza-related outcomes. To balance this, we intend to use ICD codes that have been used for a long time in influenza surveillance and are highly sensitive. Finally, we intend to use discharge codes, as they are the final primary diagnosis of the hospitalisation. However, there are delays in hospital discharge and the codification of the hospitalisation event. In order to minimise this, the retrospective study will only use end-of-season data.

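### The named adjustment set uses previous-season COVID-19 vaccination but names neither previous-season influenza vaccination nor recent hospital admission, although the study links registries for both

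*Protocol article*

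**What the plan says.** The section on potential confounding variables itemises the adjustment set in three groups.

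- Sociodemographic: "Sociodemographic variables, such as sex, age, health administrative region, and the European Deprivation Index, will be used as potential confounding factors".
- Health-seeking: "We will also consider the vaccination against COVID-19 in the previous season to account for health-seeking behaviour".
- Clinical: "The presence of chronic conditions, such as diabetes, asthma, or other chronic respiratory diseases, cancer, chronic renal disease, hypertension or other chronic cardiovascular disease", followed by obesity, hepatic and neuromuscular disease and immunodeficiency.

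The section on estimating vaccine effectiveness builds the fully adjusted hazard ratio from three classes: socioeconomic condition, comorbidity and health-seeking behaviour. The propensity score section enters baseline characteristics without listing them. The section on baseline characteristics allows for further socioeconomic or health-seeking variables but names none.

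Under Data sources, individual vaccination records "including influenza and vaccine brand dates, will be provided by the National Vaccination Registry", where registration is mandatory in both the public and private sectors. For outcomes, "the National Hospital Discharges Registry will be used to assess hospitalisation information". Entry is limited to people with health-service contact in the three years before the study period.

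Among the conditions for an unbiased propensity score analysis, the article says that "the variables affecting vaccination status and hospitalisation due to influenza-like-illness should have been measured". Of the unvaccinated, the Discussion says that "these individuals might differ from the vaccinated individuals due to their clinical profile", and it offers matching as the remedy.

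**The concern.** COVID-19 vaccination in the previous season stands in for a person's readiness to be vaccinated. Influenza vaccination in the previous season measures that readiness for the vaccine under study, yet it is not named. No recent hospital admission or other measure of recent health-care use is named either. In people aged 85 or over and in residents of long-term care facilities (LTCF), the presence of a chronic condition is an incomplete guide to frailty, and a recent admission adds to it.

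The two gaps act differently. Vaccination habit mainly threatens absolute IVE, where vaccinated people are compared with unvaccinated. Frailty can threaten both contrasts. In 2023/2024 the Background says that people in the community obtained the high-dose vaccine on prescription and with a co-payment, so the product received could follow clinical profile and use of care. Matching balances directly only what enters the score. The Discussion attributes residual confounding to variables that registries do not hold, which does not fit influenza vaccination history and may not fit admission history.

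**Working it through.** **What is named, against what is linked**

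1. Previous-season influenza vaccination is named as a covariate nowhere. The vaccination registry supplies individual influenza brand and dates. The relative IVE analysis covers 2022/2023 to 2024/2025, so the season before the absolute IVE season (2024/2025) lies within the study's own span. Using previous-season COVID-19 vaccination already needs vaccination records from before baseline.
2. Recent admission is also named nowhere. The discharge registry is linked, but only its outcome role is described, and outcomes are assessed from campaign start. That earlier admissions can be extracted is an inference.
3. The two open-ended lists cover sociodemographic variables and chronic conditions. Neither missing variable falls naturally into those classes. The health-seeking sentence is not an open list.

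**Scale**

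The article states no target effect, sample size or event count, so there is no planned figure to reproduce. The Background gives one anchor from the literature: relative IVE 11.2% (7.4% to 14.8%) against influenza-related hospitalisation, a ratio of 1 − 0.112 = 0.888.

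*E-value*, treating 1 − IVE as a risk ratio: 1/HR + √[(1/HR)(1/HR − 1)].

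- At 0.888: 1.126 + √(1.126 × 0.126) = 1.50.
- At 0.926 (7.4%): 1.37. At 0.852 (14.8%): 1.63.

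So a factor associated about 1.5-fold with both product received and outcome, beyond the listed covariates, could account for an effect of 11.2%.

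*Bias factor for one binary marker*: B = [1 + p1(RR − 1)] / [1 + p0(RR − 1)], with p1 the prevalence in the exposed and p0 in the reference group. Apparent IVE = 1 − true HR × B. **All prevalences and risk ratios below are assumptions**, and no absorption by listed covariates is allowed for.

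| Contrast | Marker, p1 vs p0 | RR | B | Apparent IVE |
|---|---|---|---|---|
| Absolute, no true effect | Recent admission, 20% vs 35% | 2 | 1.20/1.35 = 0.889 | 11.1% |
| Absolute, no true effect | Recent admission, 20% vs 35% | 3 | 1.40/1.70 = 0.824 | 17.6% |
| Absolute, no true effect | Prior influenza vaccination, 90% vs 30% | 0.7 | 0.73/0.91 = 0.802 | 19.8% |
| Absolute, no true effect | Prior influenza vaccination, 90% vs 50% | 0.9 | 0.91/0.95 = 0.958 | 4.2% |
| Absolute, no true effect | Prior influenza vaccination, 95% vs 85% | 0.7 | 0.715/0.745 = 0.960 | 4.0% |
| Absolute, no true effect | Prior influenza vaccination, 95% vs 85% | 0.9 | 0.905/0.915 = 0.989 | 1.1% |
| Relative, true 11.2% | Recent admission, 30% vs 25% | 2 | 1.30/1.25 = 1.040 | 7.6% |
| Relative, true 11.2% | Recent admission, 30% vs 20% | 1.5 | 1.15/1.10 = 1.045 | 7.2% |
| Relative, true 11.2% | Recent admission, 20% vs 30% | 1.5 | 1.10/1.15 = 0.957 | 15.1% |
| Relative, true 11.2% | Recent admission, 30% vs 20% | 3 | 1.60/1.40 = 1.143 | −1.5% |
| Relative, true 11.2% | Recent admission, 20% vs 30% | 3 | 1.40/1.60 = 0.875 | 22.3% |

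For relative IVE the shift from 11.2% is 3.6 to 4.0 points in the milder rows and 11.1 to 12.7 points in the extreme ones. Its direction depends on which product the frailer people received.

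**The case against.** The strongest reply is that unnamed is not excluded. The baseline section leaves room for further health-seeking variables, the fully adjusted model is defined by class, and the propensity score inputs are not itemised. A journal article may leave the final list to a fuller document. This stands in part: nobody can say that the study will not adjust for these variables, and the use of COVID-19 vaccination in the propensity score is itself only implied. But the article chose to itemise its covariates and named the proxy without the direct measure. The open health-seeking wording also does not obviously reach a frailty marker such as recent admission.

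A reader might infer that the bias can equal the relative IVE sought and that matching on the listed variables cannot remove it. The document does not support that. Age, deprivation, comorbidities and COVID-19 vaccination are plausibly correlated with both missing variables and would absorb part of the bias, as would the three-year contact restriction. The sizes are assumed, and everyone in the relative IVE cohort is vaccinated, so healthy-vaccinee bias belongs mainly to absolute IVE.

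A reader might also infer that nearly every participant carries a chronic-disease flag, so that the flags are useless. No figure in the article shows this, and combinations of about ten conditions can still discriminate. Adding dementia or same-season COVID-19 vaccination would be a matter of preference; dementia could fit the open list of conditions.

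On previous-season product, the objection is right. The high-dose vaccine began to be available in 2022/2023, so previous product cannot separate people in that season's analysis. Later, it may predict current product strongly enough to harm overlap, particularly in LTCF.

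Finally, the exclusion of people vaccinated before the study started would make prior vaccination irrelevant if it reached back to earlier seasons. Across three successive annual campaigns the natural reading is doses given before the campaign in question.

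**Conclusion.** The point holds as a weakness in a stated covariate set, not as a contradiction or a calculation error. Two baseline variables that bear directly on vaccination habit and frailty are unnamed, although the study links registries that should hold them. Availability is well supported for influenza vaccination and inferred for admissions before baseline. The avoidable confounding concerns vaccination habit mainly in absolute IVE, and frailty in both contrasts. Its size cannot be derived from the document: the illustrations give a few to about ten or more percentage points before any absorption by listed covariates, and as little as 1 point where prior vaccination differs little between groups. Set against the article's own anchor of 11.2%, that is enough to justify naming the variables before the data are received.

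**What to change.** - In the section on potential confounding variables, for both the fully adjusted Cox model and the propensity score, add (a) influenza vaccination in the previous season, yes/no, and (b) number of all-cause hospital admissions in the 12 months before campaign start.
- Under Data sources, state that the vaccination and discharge registries will be extracted with that look-back, subject to availability. For 2022/2023 this means vaccination records from 2021/2022.
- Use previous-season product (high versus standard dose) only in seasons after 2022/2023, and move it to a sensitivity analysis if propensity score overlap is poor.

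The cost is small: a longer extraction window, a few extra parameters and possibly fewer matched pairs. The article says that no data had been received at submission, so the extraction request could still be specified this way at that point.

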### Construction of the cohort

#### Identification of individuals and characteristics at baseline.

The reference population database will be linked with the electronic databases on vaccination, comorbidities and/or health-seeking behaviour, hospitalisations and other vital registries, using the unique identifiers through a deterministic data linkage procedure (no random component in the linkage procedure). Individuals will enter the study in their corresponding vaccination status group based on the data available in the vaccination registry.

Variables to be measured at baseline include age, sex, health administrative region, comorbidities, and other socioeconomic or health-seeking behaviour variables that will be used to adjust IVE estimates to stratify or account for confounding.

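### Pneumococcal vaccination is not named among the adjustment variables, although the secondary outcome includes pneumonia of unknown cause and linkage to the national vaccination registry is planned

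*Protocol article*

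**What the plan says.** All references are to the protocol article.

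- **Potential confounding variables for adjustment** gives three groups of variables. The first is sociodemographic: "Sociodemographic variables, such as sex, age, health administrative region, and the European Deprivation Index, will be used as potential confounding factors". The second is a single vaccination-history item: "We will also consider the vaccination against COVID-19 in the previous season to account for health-seeking behaviour". The third is a list of chronic conditions that ends with "chronic hepatic disease, neuromuscular disease, and immunodeficiency, will also be included as potential confounding factors". No vaccine other than COVID-19 is named.
- **Outcome** sets the primary outcome as J11. The secondary outcome is cardiorespiratory admission "with a secondary diagnosis of pneumonia, J12 (Viral pneumonia) and J18 (Pneumonia of unknown etiology"), and outcomes are analysed separately.
- **Data sources** takes vaccination data from VACINAS and describes registration as mandatory: "VACINAS is the national vaccination registry, that is accessible to all health professionals who administer the vaccine", in the public and private sectors alike. It specifies only influenza vaccination content. It also says that no data access had been received at submission.
- **Identification of individuals and characteristics at baseline** plans the linkage: "The reference population database will be linked with the electronic databases on vaccination, comorbidities and/or health-seeking behaviour, hospitalisations and other vital registries". It leaves room for further health-seeking variables without naming any.
- **Data sources** also restricts the cohort to people with health-service contact in the preceding three years, "to account for health seeking behaviour and likelihood to have a vaccine recommended".
- **Propensity score matching** bases the score on baseline characteristics and states the assumption of no unmeasured confounding.

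**The concern.** A confounder must be related both to the exposure and to the outcome. Pneumococcal vaccination plausibly is both. Older people who accept one vaccine are likely to accept another, so uptake may be higher among high-dose recipients than among people with no influenza vaccine. J18 is pneumonia without an identified cause, so bacterial cases can fall in it, and a vaccine that prevents some of them lowers the event rate by a route unrelated to influenza.

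The planned controls for health-seeking, previous COVID-19 vaccination and recent health-service contact, are proxies for behaviour. Neither stands in for direct protection against pneumonia.

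The Discussion attributes residual confounding to variables that registries do not hold. That reason may not apply here, since a national vaccination registry is to be linked anyway. At stake is an upward bias in absolute IVE for the secondary outcome, and possibly in relative IVE where access to the high-dose vaccine was self-selected.

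**Working it through.** The article gives no figure on this point to reproduce, and no pneumococcal coverage or effect. Every input below is therefore an assumption, varied over a range.

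**Formula.** Let p1 and p0 be the proportions with pneumococcal vaccination in the high-dose and reference groups. Let e be the proportional reduction in the whole outcome associated with it. If the high-dose vaccine has no effect, the apparent hazard ratio is approximately

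B = (1 − p1·e) / (1 − p0·e),

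and the spurious IVE is 1 − B.

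**Central case, e = 0.10**

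- Absolute IVE, 50% versus 20%: B = 0.95/0.98 = 0.969, so 3.1 points.
- Absolute IVE, 40% versus 25%: B = 0.96/0.975 = 0.985, so 1.5 points.
- Relative IVE, 50% versus 40%: B = 0.95/0.96 = 0.990, so 1.0 point.
- Relative IVE, equal uptake: B = 1, so 0 points.

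**Range over e**

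| Comparison | p1 vs p0 | e = 0.05 | e = 0.10 | e = 0.15 |
|---|---|---|---|---|
| Absolute | 50% vs 20% | 1.5 | 3.1 | 4.6 |
| Absolute | 40% vs 25% | 0.8 | 1.5 | 2.3 |
| Relative | 50% vs 40% | 0.5 | 1.0 | 1.6 |

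**Wider inputs.** If pneumococcal vaccination is also allowed to mark health-seeking, the association can be set stronger, with risk ratios from 0.95 to 0.70. At 60% versus 30% the spurious absolute IVE then runs from 1.5 to 9.9 points. At 70% versus 20% it runs from 2.5 to 16.0. The health-seeking part of that association is what the existing covariates are meant to remove, so these are crude figures.

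**Direction.** The sign is not fixed. If pneumococcal vaccination goes to frailer people and on balance marks a 10% higher risk, the 50% versus 20% case gives B = 1.05/1.02 = 1.029, and a null IVE would read −2.9 points.

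**Scale.** The Background cites a relative IVE of 11.2% (7.4% to 14.8%). One point is about a tenth of that (1.0/11.2 = 0.09). With a true 11.2% and B = 0.990, the observed value would be 1 − 0.888 × 0.990 = 12.1%. The cited figure is for influenza-related hospitalisation, not for the pneumonia outcome, so it serves only as a yardstick.

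**The case against.** The strongest reply is that this is an absence from an open list. The sociodemographic and chronic-condition variables are given as examples, the baseline section allows for further health-seeking variables, and the full adjustment is defined by domain. The final covariate list may stand in a document not shown. This stands in part: a reader might infer that pneumococcal vaccination is excluded from the Cox model and the propensity score, and the article does not say so. It does name vaccination history specifically, though, and names only COVID-19.

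A reader might also infer that the registry is already linked and that pneumococcal records are at hand. Linkage is only planned, and the article does not say whether adult pneumococcal doses are recorded or how completely.

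Third, a reader might infer a bias that always raises IVE. The documents do not support a fixed direction, as the working shows.

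Fourth, the reach is narrow. The outcome is secondary. Its J12 part is viral pneumonia, where direct pneumococcal protection is least plausible, and that share dilutes any reduction confined to J18. For relative IVE both groups are vaccinated, so an imbalance needs a specific reason. The prescription and co-payment route described in the Background concerns community access in 2023–2024. The high-dose vaccine was free in long-term care from 2022–2023 and free from age 85 in 2024–2025, the only season used for absolute IVE.

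Finally, the three-year contact restriction, the COVID-19 covariate, age, deprivation and comorbidities will absorb part of any imbalance, and the Discussion discloses residual confounding in general. All of this reduces the concern. None of it accounts for direct protection against pneumonia.

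**Conclusion.** The point holds as a modest, low-cost improvement. It is not an error that undermines the study. A plausible confounder of the pneumonia outcome is not named, and the planned linkage to the national vaccination registry may make it obtainable. The concern applies mainly to absolute IVE on the secondary outcome, chiefly its J18 part. It extends to relative IVE only where pneumococcal uptake differs between the vaccine groups, which is possible for community recipients in 2023–2024 but is not shown.

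Under a 10% reduction and the coverage gaps assumed above, the spurious effect is about 1.5 to 3.1 points for absolute IVE and about 1.0 point for relative IVE, before absorption by the planned adjustment and restriction. These figures rest on higher pneumococcal uptake among high-dose recipients and on a protective net association. The documents establish neither, so the figures illustrate the possible bias and do not estimate it. The documents also give no basis for extending the calculation to the primary outcome.

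**What to change.** In the section on potential confounding variables, add ever-receipt of a pneumococcal vaccine (yes/no), dated before the start of the campaign and requested from VACINAS. Include it in the fully adjusted Cox model and in the propensity score, at least for the secondary outcome.

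If the field cannot be obtained or proves incomplete, say so in the limitations. Then report a simple quantitative bias analysis with the formula above, over stated ranges for coverage and effect.

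The cost is one more field in a data request for which access had not been received at submission, and one model term. Cohorts, outcomes and effect measures stay as they are. The main drawback is that older doses may be under-recorded. People without a record would then be classed as never vaccinated, and some confounding would remain.
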